### Study population

#### Eligibility and enrolment

Patients with active relapsing-remitting and active progressive MS, diagnosed according to most recent McDonald criteria,^39 40^ and who are not eligible for or do not want to be treated with currently available DMT, will be recruited. Patients are included after written informed consent and enrolled in the study when the inclusion and exclusion criteria are met (table 2).

**Table 2 T2:** Inclusion and exclusion criteria. All the inclusion criteria must be fulfilled. The presence of any of the exclusion criteria shall exclude the patient

Inclusion criteria	Exclusion criteria
MS according to most recent McDonald criteria	Previous use of immunosuppressive or cytostatic treatment, including mitoxantrone, cladribine, alemtuzumab or bone marrow transplantation or stem cell transplantation at any time prior to enrolment
Age 18–60 years	Treatment with fingolimod or natalizumab or dimethylfumarate in the past 12 weeks or teriflunomide within the past 15 weeks or ocrelizumab/rituximab within the past 6 months prior to the first administration
EDSS of 0–6.5 inclusive	Pregnancy or planning pregnancy in the next 12 months and breast feeding
First signs or symptoms at least 3 months prior to enrolment in the study	Drug or alcohol abuse
Active MS (relapsing and/or progressive): one relapse in the past year and/or at least one enhancing lesion on brain MRI in the past year; at least one new or enlarging T2 lesion in comparison with a reference scan from maximum 1 year before	Inability to undergo MRI assessments
Normal peripheral B-cell count after treatment with ocrelizumab	
No evidence of relapse for at least 30 days prior to start of screening and throughout during the screening phase	History of or actual signs of immunodeficiency or malignancies
Positive T cell reactivity response to a mix of seven myelin-derived peptides	Concurrent clinically relevant cardiac, immunological, pulmonary, neurological, renal or other major disease
Able to sign informed consent and comply with the protocol assessments	Active or chronic infection (hepatitis B or C, HIV, syphilis or tuberculosis)
No wish to be treated with currently available DMT	Splenectomy
Appropriate venous access and *adequate cervical lymph nodes on ultrasound mapping	

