#### Immune-monitoring

To evaluate therapy-related changes in the immune cell profile, peripheral blood (10×10 mL heparin tubes) will be sampled according to the time points depicted in figure 1 and table 3, and analysed by multiparameter flow cytometry prior to, during and after vaccination. In an attempt to cover the main leucocyte subsets of peripheral blood, the following subsets and their activation status will be enumerated in whole blood samples: CD4^+^ and CD8^+^ T cell subpopulations, B cell subsets, natural killer (NK) cells, NKT cells and myeloid cells. Myelin-specific T cell reactivity will be determined before, during and after completion of administration of tolDC. For this, responsiveness of T cells to myelin antigens will be investigated. As a control, the responsiveness of T cells to unrelated antigens, for example, cytomegalovirus or tetanus toxoid, will be addressed. In doing so, we will be able to assess ex vivo the potential risk of inducing opportunistic infections by administering tolDC to MS patients. Finally, patient materials from the studies will be specifically biobanked. We envisage to maximally performing batch measurements and centralised immune monitoring analysis as soon as a dose cohort has reached 3 months follow-up of all patients. For this, extensive immune cell profiling as well as cytokine production of T cells will be analysed by multiparameter flow cytometry. Using lineage-specific as well as activation markers, proportions and activation status of the different immune cell subsets will be determined. Besides, antibody titers and memory B cell analysis will be performed.

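### Table 2 requires a normal B-cell count after ocrelizumab but not after rituximab, although the two drugs share one 6-month washout

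*Protocol article*

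**What the plan says.** Two rows of Table 2 (Protocol article, Eligibility and enrolment) bear on earlier anti-B-cell treatment.

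- The exclusion column bars treatment with "ocrelizumab/rituximab within the past 6 months prior to the first administration". The two drugs are named together, with the same interval.
- The inclusion column asks for "Normal peripheral B-cell count after treatment with ocrelizumab". Rituximab is not named here, and no other row asks for a B-cell count.

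Two general exclusions lie close to the point: "History of or actual signs of immunodeficiency or malignancies", and "Previous use of immunosuppressive or cytostatic treatment, including mitoxantrone, cladribine, alemtuzumab or bone marrow transplantation or stem cell transplantation at any time" before enrolment. Neither mentions B cells or rituximab.

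The Immune-monitoring section gives the aim "To evaluate therapy-related changes in the immune cell profile" and counts "CD4^+^ and CD8^+^ T cell subpopulations, B cell subsets, natural killer (NK) cells, NKT cells and myeloid cells" before, during and after vaccination. It adds that "antibody titers and memory B cell analysis will be performed". MRI is compared within patients, pretreatment against later scans (MRI acquisition and evaluation), and MRI lesions and relapses also form part of the primary safety assessment (Safety). Both trials are open-label dose escalations, and no untreated control arm is described (Study design).

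**The concern.** Table 2 treats the two drugs alike for elapsed time and differently for B-cell status. Take two patients, each 6.5 months past the last dose and each still B-cell depleted. The one who had ocrelizumab fails an inclusion criterion. The one who had rituximab fails no criterion that names B cells.

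If the second patient is enrolled, two readings become harder.

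- **Immune outcomes.** B cells that return during the vaccination and follow-up period would move B-cell subsets, and possibly memory B cells and antibody titres, in the same window in which a tolDC effect is sought. With no control arm, the two causes cannot be separated in that patient.
- **Safety by MRI and relapse.** Frequent MRI is there to pick up unexpected disease activity promptly. If some effect of the earlier drug persists, it could hide such activity early on, and its fading could resemble late activity.

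**Working it through.** The point concerns eligibility wording, so no power or error-rate formula applies. The check has three parts.

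**1. Do other rows close the gap?**

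| Row in Table 2 | Could it exclude a depleted rituximab patient? | Why it does not clearly do so |
|---|---|---|
| Immunodeficiency exclusion | Possibly, on the investigator's judgement | If it covered drug-induced B-cell depletion, the ocrelizumab row would be redundant |
| Lifetime exclusion for immunosuppressive treatment | Possibly, if rituximab is classed that way | Rituximab would then be barred for life and its 6-month washout would have no function; it is not among the named examples |
| Active MS within the past year | Makes entry of a fully suppressed patient less likely | The one-year look-back exceeds the 6-month washout, so the qualifying activity may pre-date the last rituximab dose |
| Positive T-cell reactivity to myelin peptides | No | It does not measure B cells |

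None is an explicit B-cell check after rituximab.

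**2. Is there time for recovery to overlap with the readouts?**

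Table 4 places immunomonitoring at V1, one week after V4, one week after V6, and at F3. Figure 1's legend puts V6 at week 14 and F3 three months (about 13 weeks) after the last treatment. The window is therefore about 14 + 13 = 27 weeks, roughly six months. The V1 sample would show depletion that is already present. It cannot say whether a later rise is recovery from rituximab or an effect of tolDC.

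**3. How much weight does one patient carry?**

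Inputs: three cohorts of 3, each expandable to 5 (Table 3).

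- The plan's own total: 3 × 3 = 9 and 3 × 5 = 15, which reproduces the stated 9–15.
- Share of one patient: 1/3 = 33% and 1/5 = 20% of a cohort; 1/9 = 11% and 1/15 = 6.7% of a trial.

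The article does not give the proportion of entrants with previous rituximab. If that proportion is *p*, the chance of at least one in a trial of *n* is 1 − (1 − *p*)^*n*. The values of *p* below are assumptions for illustration.

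| Assumed *p* | *n* = 9 | *n* = 15 |
|---|---|---|
| 2% | 17% | 26% |
| 5% | 37% | 54% |
| 10% | 61% | 79% |
| 20% | 87% | 97% |

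These are chances of previous rituximab use. The chance of a patient who is also still depleted at entry is lower, and the article gives no figure from which to derive it.

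**The case against.** The strongest reply is that the mismatch has little practical consequence, for five reasons.

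- **Visibility.** B-cell subsets are counted at V1, so an abnormal baseline in one of 9 to 15 patients would be seen. The Analysis section plans no confirmatory testing, treats p-values cautiously and draws on all the evidence for each patient. This stands as a reason for low severity. It does not stand as a remedy, because a visible low baseline does not identify the cause of a later rise.
- **Investigator's judgement.** The immunodeficiency exclusion could be applied to persistent depletion. That is true, but it leaves the outcome to each site, and the ocrelizumab row shows that the table does not rely on it for that drug.
- **No stated rationale.** The table does not explain its B-cell row, and fingolimod, natalizumab, dimethylfumarate and teriflunomide have time-only washouts too. It cannot therefore be asserted that the authors judged 6 months insufficient. This stands. The point rests on unequal treatment of two drugs joined in one row, not on an inferred motive.
- **Outside knowledge.** The article does not say how long depletion lasts after rituximab, or how far it suppresses lesions or relapses. This also stands, so the harm is stated as possible only.
- **Scope.** The secondary objectives centre on lymphocyte phenotyping, cytokines and myelin-specific T-cell reactivity; B cells are one subset among several.

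A reader might infer more: that such patients will be enrolled, that their B-cell course will be reported as a tolDC effect, that one near-zero baseline will dominate percent changes, or that the comparison of routes is distorted. The documents do not support these. The first two need a chain of events for which no figures are given. No percent-change measure is planned for B cells. Nothing suggests that rituximab use differs between the two countries, and the article already acknowledges that non-randomisation limits the comparison of routes.

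**Conclusion.** The inconsistency is real: two drugs sharing one washout face different B-cell requirements, without a stated reason, and no other row clearly removes the difference. A still-depleted patient more than 6 months past rituximab may enter, and that patient's B-cell recovery could be mistaken for a tolDC-related change. Any residual drug effect could blur the MRI and relapse component of safety, which also informs the judgement that a cohort's results are satisfactory for escalation.

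The effect is confined to however many such patients enrol, each being one third of a minimum cohort. The DLT counting rule, the feasibility endpoint and the sample size are untouched. The conclusion assumes that at least one rituximab-pretreated patient is enrolled and that depletion can outlast the washout; the article gives a figure for neither. It is a cheap improvement of minor severity.

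**What to change.** Reconcile the two Table 2 rows in both trials so that the drugs sharing the washout are handled consistently with respect to the B-cell count, or add a sentence saying why they differ. Which eligibility rule applies is the sponsor's decision; the documents show only that the rows disagree. If a count is required, it can use the blood already drawn at screening or baseline (T0).

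Show the B-cell and disease-activity results of any rituximab-pretreated entrant separately, so that a reader can see whether a cohort's pattern depends on that patient.

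The cost is a phrase in Table 2 and, where applicable, a line in the report. The downside, if the check is extended, is that an occasional patient is delayed or not enrolled.

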#### Determination of sample size and dose-escalation procedure

The studies will be conducted according to a ‘best of five’ design,^41^ an alternative of the traditional 3+3 design in that one additional patient is added when one or even two dose-limiting toxicities (DLT) are observed among the first three patients. Another patient is added when two DLT are observed among four treated patients. Dose escalation is allowed if DLT are observed among none of three, one of four or two of five patients, but the trial will terminate if three or more DLT are observed. A DLT is defined as a serious adverse event (SAE) that is attributable to the study cells administered, or of which the severity prevents further escalation. Dose escalation decisions will be made after all subjects in the cohort have completed at least 3 months of follow-up and when the results of the safety and tolerability analyses of the preceding dose regimen are satisfactory in the judgement of the investigators and the independent Data Safety Monitoring Board (DSMB).

An overview of the dose escalation is provided in table 3. Altogether, each phase I study is intended to accrue a total number of 9–15 evaluable patients.

**Table 3 T3:** Outline of the cell doses and patient numbers, per phase I clinical trial, in the dose escalation cohorts for intradermal and intranodal administration of tolDC

Cohort	Treatment regimen	Patient numbers
1	6 i.d./i.n. injections of 5×10^6^ tolDC	N=3 (+1+1)
2	6 i.d./i.n. injections of 10×10^6^ tolDC	N=3 (+1+1)
3	6 i.d./i.n. injections of 15×10^6^ tolDC	N=3 (+1+1)

N, number; i.d., intradermal; i.n., intranodal; tolDC, tolerogenic dendritic cells.

### Study medication

Generation of tolDC will be carried out according to the principles and guidelines of GMP laid down in Directive 2003/94/EC. TolDC production will be performed in the GMP facilities of the Center for Cell Therapy and Regenerative Medicine of the Antwerp University Hospital (Belgium) and of the Cell Therapy Area of the Clínica Universidad de Navarra (Spain).

Clinical-grade autologous tolDC will be prepared from a leukapheresis. CD14^+^ monocytes will be cultured in GMP-grade cell culture medium supplemented with 2% human AB serum, granulocyte macrophage colony-stimulating factor, interleukin (IL)−4 and 1α,25 dihydroxyvitamin D_3_. At day 4, tolDC will be stimulated using an inflammatory cytokine cocktail, consisting of tumour necrosis factor-α, prostaglandin E_2_ and IL-1β. At day 6, tolDC will be harvested, loaded with seven myelin antigens (MBP_13-32_, MBP_111-129_, MBP_154-170_, PLP_139-154_, MOG_1-20_, MOG_35-55_ and MBP_83-99_), and cryopreserved at −196°C. Separate aliquots of the cell product will be prepared for quality control and quality assurance. This includes (i) sterility testing, (ii) cell count, (iii) viability, (iv) flow cytometric phenotyping and (v) induction of T cell hyporesponsiveness in an allogeneic mixed leucocyte reaction.

### Trial intervention: tolDC administration

In this study, six vaccine doses will be administered to each participant according to the following immunisation schedule: a total of six vaccine doses (V), with V_1-4_ at biweekly (±3 days) intervals and V_5-6_ at monthly intervals (±3 days). A complete overview of the study design is depicted in figure 1. Detailed assessments per visit are shown in table 4.

**Figure 1 F1:**
[figure not shown]
Study design. Treatment will start at V_1_, approximately 4 weeks after the leukapheresis. Patients will receive additionalinjections on week +2 (V_2_), week +4 (V_3_), week +6 (V_4_), week +10 (V_5_) and week +14 (V_6_). Patients will have follow up visits one month, and 3, 6 and 12 months following the last study treatment.

**Table 4 T4:** Study calendar. The different visits, examinations, tests and the tolDC administration are detailed on the tabular study schedule overview.

	Screening		Treatment period							Safety follow-up			
	Ts	Baseline (T0)	V1	V1 +1 day	V2	V3	V4	V5	V6	F1	F3	F6	F12
Informed consent	·												
Inclusion and exclusion criteria	·												
IFN-γ EliSPOT (T cell reactivity assay)	·		·				·+1w		·+1w		·		
Leukapheresis		·											
TolDC preparation		·											
TolDC treatment			·		·	·	·	·	·				
Patient evaluation:													
Vital signs (HR, BP, …)	·	·	·		·	·	·	·	·	·	·	·	·
ECG	·	·	·		·	·	·	·	·	·	·	·	·
Blood analysis for safety (1×5 mL EDTA tube and 2×10 mL serum tubes)	·	·	·		·	·	·	·	·	·	·	·	·
Urine pregnancy test	·	·	·		·	·	·	·	·	·	·	·	·
Full neurological examination (EDSS, 9-HPT, T25FW, SDMT, MSQOL-54)	·		·										
Pain score after treatment injection			·		·	·	·	·	·				
MRI	·	·	·		·		·+1w	·+1w	·+1w		·	·	·
Immunomonitoring (10×10 mL heparin tubes+1 serum tube)			·				·+1w		·+1w		·		
Biobanking for follow-up immunomonitoring													
(Serious) Adverse events and concomitant medication	Continuous												

BP, Blood Pressure; ECG, Electrocardiogram; EDSS, Expanded Disability Status Scale; 9-HPT, 9 Hole Peg Test; MRI, Magnetic Resonance Imaging; MSQOL-54, Multiple Sclerosis Quality of Life-54; SDMT, Symbol Digit Modalities Test; T25FW, Timed 25 Foot Walk; tolDC, tolerogenic dendritic cells.

In Belgium (MS-tolDC), tolDC vaccination occurs through intradermal injection at five alternating sites (100 µL/site) in the posterior neck region to ensure lymphatic drainage to superficial and deep cervical lymph nodes (5–10 cm from the cervical lymph nodes). In addition, in Spain (TOLERVIT-MS), an expert physician will inject tolDC directly in the cervical lymph nodes under echographic guidance. If the patient’s anatomical conditions do not allow it (eg, small lymph nodes), the vaccine will be distributed in more nodes (max. 500 µL/node).

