### Secondary outcome measures

#### Clinical evaluation

The following clinical and laboratory assessments will be performed during a complete physical examination: vital signs, ECG, routine blood and urine samples, urine pregnancy test in female patients of reproductive potential and serological screening tests, according to the study schedule (figure 1 and table 4). Concurrent drug use or new AE will be reviewed and recorded.

EDSS is based on a standardised neurological examination and measures impairments in eight functional systems, including vision, brainstem, pyramidal, cerebellar, sensory, bowel and bladder, mental (cerebral) and ambulation. It has been used for over 20 years as a clinical outcome measure of MS disease progression and consists of a 10-point scale of disease severity ranging from 0, that is, no disability, to 10, that is, death from MS.^42^ All neurologists involved in patient evaluation will be EDSS training certified.

EDSS will be supplemented by three well-known, quantitative, continuous tests that evaluate ambulation (walking speed by the timed 25 foot walk test or T25FW, arm dexterity and function by the 9 Hole Peg Test or 9-HPT, and cognition by the Symbol Digit Modalities Test or SDMT).

The effect on disability progression will be characterised by reporting the proportion of patients who are free from disease progression. For this, disability will be assessed based on a sustained clinically relevant change seen in any one of the disability assessments: EDSS, T25FW, SDMT or the 9-HTP. Disease progression is defined by: 3-month sustained increase from baseline in the EDSS score (1 point in patients with baseline EDSS score 0 to 5.0; 0.5 point in patients with baseline EDSS score of 5.5–6.5) or 3-month sustained increase of at least 20% from baseline in the time taken to complete the T25FW or 3-month sustained increase of at least 20% from baseline in the time taken to complete the 9-HPT. Percent change from baseline after treatment in SDMT score will also be recorded.

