### Analysis

Given the design of the study (phase I) and its specific primary end point (safety), no confirmatory statistical testing will be performed. P-values will be calculated but interpreted with caution. Study investigations will be exploratory and conclusions will be based on the complete set of patient evidence.

Analyses of safety variables will be performed with the safety population (all the patients treated with at least one dose of the cell product) by available data only analysis. For demographic and safety analysis, that is, the incidence of AE, laboratory values and changes in vital signs, descriptive statistics will be calculated including frequencies for categorical variables and mean and SD, or median and IQR for quantitative parameters. In brief, EDSS and other repeatedly measured variables will be analysed by means of Mixed Models for Repeated Measurements. In case model assumptions are violated (eg, non-Gaussian errors) or when dealing with ordinal efficacy variables, alternative methods (including non-parametric methods and ordinal regression methods for repeated measurements) will be used. The percentage of patients with 1-point in EDSS improvement will be estimated using a binomial regression model including the treatment and the baseline EDSS. The remainder of variables will be analysed according to the appropriate statistical test: χ^2^ or Fisher’s exact test to compare categorical variables, the dependent or independent t-test for continuous Gaussian-distributed variables and the Wilcoxon or Mann-Whitney test for ordinal and non-Gaussian continuous data. The significance level alpha will be set at 0.05 for two-tailed analysis. Variables to assess the analysis of secondary and tertiary outcome measures will be performed with per protocol population. Continuous variables as a minimum will be described by number of total and non-missing observations (n) and the appropriate location-scale statistics including arithmetic mean, SD, minimum, median, Q1–Q3 and maximum. Categorical variables will be presented using the number of non-missing observations (n) or the number of patients in the population (N) as applicable and percentages (%). Two-sided 95% (exact) CI will be provided when relevant.

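### As printed, the study calendar schedules no neurological examination or MSQOL-54 after V1, though the outcomes need them; separately, the role of SDMT in the progression definition is ambiguous

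*Protocol article*

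**What the plan says.** The section on tolDC administration gives Table 4 the status of the per-visit schedule: "Detailed assessments per visit are shown in table 4". In that table the row "Full neurological examination (EDSS, 9-HPT, T25FW, SDMT, MSQOL-54") carries marks at Ts and V1 and nowhere else.

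Four other parts of the article rely on examinations after V1:

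- **Clinical evaluation (secondary outcomes).** "The effect on disability progression will be characterised by reporting the proportion of patients who are free from disease progression". The EDSS component is a "3-month sustained increase from baseline in the EDSS score". The T25FW and 9-HPT components are 3-month sustained increases of at least 20%.
- **Analysis.** "EDSS and other repeatedly measured variables will be analysed by means of Mixed Models for Repeated Measurements". A binomial model for a 1-point EDSS improvement is also planned.
- **Patient reported outcome measurements.** MSQOL-54 is used to detect changes in quality of life. It sits in the same Table 4 row.
- **Safety (primary outcome).** Neurological examination, covering relapses and worsening disability, is one of the ways adverse events are picked up.

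On SDMT, Clinical evaluation first bases disability on a sustained change "seen in any one of the disability assessments: EDSS, T25FW, SDMT or the 9-HTP". The definition that follows has EDSS, T25FW and 9-HPT components only, and then adds: "Percent change from baseline after treatment in SDMT score will also be recorded".

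**The concern.** A 3-month sustained change needs a visit at which the worsening is first seen and a second visit at least 3 months later that confirms it. A repeated-measures model needs repeated measures. A change in MSQOL-54 needs a value after treatment. The printed calendar provides none of these. It also leaves open which visit is the baseline, because the column with that name has no neurological examination while Ts and V1 both do.

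An examination not done at a visit cannot be recovered afterwards. The two trials are also meant to be compared on harmonised assessments. If each site fills the gap with its own choice of visits, the chance to observe and confirm progression will differ between the intradermal and the intranodal trial.

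The SDMT wording is a separate and smaller matter. Two analysts with identical data could report different progression-free proportions, depending on which sentence they follow.

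**Working it through.** The article gives no figure for this outcome to reproduce. The check is a count of Table 4 cells set against what the text requires.

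**1. Marks in Table 4.** There are 13 visit columns: Ts, T0, V1, V1 +1 day, V2 to V6, F1, F3, F6, F12. Ten of them come after V1.

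| Row | All marks | Marks after V1 | Where, after V1 |
|---|---|---|---|
| Full neurological examination and MSQOL-54 | 2 | 0 of 10 | none |
| Vital signs | 12 | 9 of 10 | V2–V6, F1, F3, F6, F12 |
| MRI | 10 | 7 of 10 | V2, V4, V5, V6, F3, F6, F12 |
| IFN-γ ELISPOT | 5 | 3 of 10 | V4, V6, F3 |

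The neurological row has its full 13 cells, and other rows keep their later marks. This argues against marks having been lost when the table was read.

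**2. What confirmation requires.** The visit times come from the Figure 1 caption: V2 to V6 at weeks 2, 4, 6, 10 and 14 after V1, then "Patients will have follow up visits one month, and 3, 6 and 12 months following the last study treatment". Taking 3 months as 13 weeks:

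- F3 = 14 + 13 = week 27
- F6 = 14 + 26 = week 40
- F12 = 14 + 52 = week 66

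The number of pairs of scheduled post-V1 examinations at least 13 weeks apart is:

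- as printed: 0 examinations, hence 0 pairs;
- with examinations at F3, F6 and F12: 3 pairs (F3–F6, 40 − 27 = 13 weeks; F6–F12, 66 − 40 = 26 weeks; F3–F12, 66 − 27 = 39 weeks);
- with V6 added: 6 pairs, the new ones being V6–F3 (13 weeks), V6–F6 (26) and V6–F12 (52).

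Existing visits are therefore enough. The F3–F6 and V6–F3 intervals meet the 3-month requirement with nothing to spare on nominal dates.

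**3. SDMT.** The lead-in sentence has four components (EDSS, T25FW, SDMT, 9-HPT). The definition has three, each with a numeric threshold. SDMT has no threshold anywhere. The sample-size section gives 9 to 15 evaluable patients per trial. The weight of one patient whose classification turns on SDMT is:

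- 1/15 = 6.7 percentage points
- 1/9 = 11.1 percentage points

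The documents give no rate at which patients worsen on SDMT alone, so the number of patients affected cannot be estimated.

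**The case against.** The strongest reply is that the finding rests on blank cells in a table whose blanks are not all literal. The biobanking row has no mark at any visit, although the Immune-monitoring section says patient materials will be biobanked, and the V1 +1 day column is empty throughout. Figure 1 belongs to the schedule and is not shown. The article also condenses two trials whose full protocols are not at hand. All of this stands, and it limits the claim to the schedule as printed.

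A reader might infer that the trials will collect no disability or quality-of-life data after treatment. The documents do not support that. The Safety, Clinical evaluation and Analysis sections plainly intend later examinations, and sites may work from protocols that schedule them.

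A reader might also infer that relapses cannot be judged. That goes too far: patients are to be examined within 7 days of symptom onset, and V1 (or Ts) supplies a previous EDSS for a first relapse. Those examinations do not rescue the progression outcome, however, because they are unscheduled, arise only in patients with symptoms and carry no 3-month confirmation visit.

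Nor does the SDMT conflict make progression uncomputable. The three-component definition works by itself, and the lead-in can be read as loose wording.

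Finally, disability progression and MSQOL-54 are not primary endpoints, no confirmatory testing is planned, and dose escalation depends on dose-limiting toxicities and on the judgement of the investigators and the DSMB, not on sustained progression. This lowers the severity. It does not remove the contradiction, because a visit-by-visit calendar that disagrees with the outcomes in the same article is not a detail left out by condensing.

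**Conclusion.** The point holds in two parts.

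- **Calendar.** Table 4 as printed contradicts the Clinical evaluation, Analysis, Patient reported outcome and Safety sections. With 0 scheduled post-V1 examinations against a minimum of 2 for confirmed progression, the progression-free proportion, the EDSS models, the 1-point improvement analysis and the MSQOL-54 change cannot be computed from that schedule. The baseline visit is not identifiable from it either. This assumes that the row was read correctly; its complete cell count supports that, but it should be checked against the published table, Figure 1 and the two full protocols.
- **SDMT.** The outcome is ambiguous, not uncomputable. Each patient whose status turns on SDMT is worth about 7 to 11 percentage points in a trial of 15 to 9 patients, taking all evaluable patients as the denominator.

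Severity is moderate. The likeliest cause is an omission in the calendar, and it mainly affects secondary, exploratory outcomes. Worsening disability also feeds the safety assessment, which is a reason to correct it and not let it pass, but the documents do not show that the primary safety evaluation or the escalation decisions fail because of it.

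**What to change.** 1. Check the neurological-examination row of Table 4 against the full protocols and Figure 1. Then reconcile it with the four text sections by marking the examination and MSQOL-54 at existing post-treatment visits that allow 3-month confirmation, for example F3, F6 and F12. Use the same visits in both trials.
2. Name the visit that serves as baseline for EDSS, T25FW, 9-HPT, SDMT and MSQOL-54.
3. Settle SDMT in one sentence: either delete it from the list of assessments in which any one sustained change counts and keep its percent change as a separate description, or give it a numeric 3-month sustained threshold inside the definition.

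The cost is a corrected calendar row, one or two sentences of text, and some added time at visits that already exist. No new visits are needed, and the article already states that the evaluating neurologists will be EDSS certified. If the full protocols already schedule these examinations, items 1 and 2 reduce to correcting the printed table.
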